### Trial design

2.1

The present study protocol is a prospective single-center crossover randomized control trial designed to determine the effect of personalized tDCS electrode positioning on the activation of the cortical region responsible for finger movement in patients with stroke. The crossover design will be divided into six groups (four groups of eight participants each and two groups of nine participants each). All participants will randomly receive one session of conventional-active, optimized-active, or sham tDCS. After a 24-h washout period, the groups will cross to receive a different tDCS intervention until each group receives all three alternatives. Figure 1 provides a detailed explanation of this procedure and Table 1 displays the activities to be completed at each visit during the trial.

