#### Sample size

2.3.3

G*Power 3.1.9.7 (Franz Faul, Kiel, Germany) was used to determine the sample size. It was calculated based on the effect size determined by Lee et al. in 2015 for the pre-and post-tDCS intervention and MEP amplitude results (Lee et al., 2015). It was calculated using analysis of variance (ANOVA): repeated measures, within-between interaction, with a Type I error rate of 5% and a power of 95%, and with an effect size f of 0.2193764. Consequently, a sample size of 45 participants was required to determine the effectiveness of the intervention. A dropout rate of 10% was considered. Accordingly, 50 participants will be recruited for this study.

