#### Motor-evoked potential

2.6.1

In this study, MEP will be induced by the application of TMS over the M1 after positioning the center of the coil at 45° lateral to the sagittal midline (Muellbacher et al., 2000). An optimal TMS position is chosen to record the maximum potential amplitude of the abductor pollicis brevis (APB), identified as the hotspot area, which will be called conventional hotspot area for this trial (Muellbacher et al., 2000). The stimulation intensity of the M1 is determined by motor threshold, which is the intensity at which the first potential or muscle contraction occurs, starting at 40% of the maximum intensity of the stimulator and is increased by 5%.

The MEP amplitude and latency will be assessed. Latency is defined as the period from the start of a single-pulse TMS to the emergence of a wave peak in milliseconds, whereas amplitude is the distance from the baseline to the wave peak in microvolts (Lee et al., 2015).

The MEP is assessed immediately before and after each tDCS session. Hence, each group will be assessed six times over the course of the trial by investigators who are blinded to the group allocation.

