#### Primary outcome

2.6.2

The difference between groups in MEP amplitude recorded before and after each tDCS session (optimized-active, conventional-active and sham tDCS) over the M1 hand-knob area selected by the investigator on the 3D brain model of the tES LAB.

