### Statistical analyses

2.7

The results of the outcome assessment analysis will be presented as mean, standard deviation (SD), standard error (SE), and confidence interval, with the statistical significance threshold set at *p* < 0.05. The Shapiro–Wilk test will be employed to assess the normality of the data. If normality is met, a repeated measures ANOVA test will be used for within-and in-between groups analysis, and Tukey’s test will be used for *post hoc* analyses. If normality is not met, the Friedman test will be used with the Wilcoxon rank-sum test to compare independent variables. Additionally, the correlation between the pre-post MEP conventional hotspot and the M1 hand-knob area selected by the investigator on the 3D brain model of the tES LAB with the E-field generated at the structural M1 hand-knob area will be analyzed.

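### The non-parametric fallback follows a matched Friedman test with the unpaired Wilcoxon rank-sum test, although every session and pre/post contrast is within-participant; any power loss depends on a correlation the protocol does not give

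*Protocol article*

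**What the plan says.** Section 2.7 (Statistical analyses) uses a Shapiro–Wilk test to choose between two routes. The parametric route is a repeated-measures ANOVA followed by Tukey's test. The other route is: "If normality is not met, the Friedman test will be used with the Wilcoxon rank-sum test to compare independent variables".

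The design sections settle which observations are paired:

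- Section 2.1 (Trial design): "the groups will cross to receive a different tDCS intervention until each group receives all three alternatives".
- Section 2.6.1 (Motor-evoked potential): "The MEP is assessed immediately before and after each tDCS session", so that "each group will be assessed six times over the course of the trial".
- Section 2.6.2 (Primary outcome): "The difference between groups in MEP amplitude recorded before and after each tDCS session". The three sessions are then listed, so what is compared is the stimulation type.

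The hypothesis in the abstract and in section 3 is pairwise and directional: a larger MEP increase with optimized stimulation than with conventional and with sham.

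**The concern.** The rank-sum test derives its null distribution from two samples of different, unrelated people. For the treatment question this trial has no such samples: optimized, conventional and sham values come from the same participants, and so do the values before and after a session. The sentence is also inconsistent in itself, because the Friedman test needs matched blocks and its follow-up assumes there are none.

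The follow-up matters because a Friedman test can show only that some session differs. Whether optimized placement beats conventional placement or sham is left to the pairwise test, and on this route the rank-sum test is the only one named. MEP amplitude at the hand-knob, the primary outcome, can reach this route through the normality check. If the paired values are positively correlated, the unpaired test uses too large a variance, and a real advantage of optimized placement could be missed.

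**Working it through.** **Step 1. The plan's own figure.** Section 2.3.3 (Sample size) bases the calculation on "analysis of variance (ANOVA): repeated measures, within-between interaction". It sets α at 5%, asks for 95% power, takes f = 0.2193764, and concludes that "a sample size of 45 participants was required to determine the effectiveness of the intervention". It does not give the number of groups k, the number of measurements m, the correlation ρ or the sphericity correction ε. I assume k = 3, m = 6, ρ = 0.5 and ε = 1:

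- λ = f²·N·m/(1 − ρ) = 0.2193764² × 45 × 6 / 0.5 = 25.99
- df1 = (k − 1)(m − 1) = 10; df2 = (N − k)(m − 1) = 210
- Power = 0.954. With N = 42 it is 0.937, so 45 is the smallest multiple of three that reaches 95%.
- 45 / 0.9 = 50, as stated.

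The figure reproduces, but not uniquely: k = 3, m = 2, ρ = 0.75 also gives 45. The stated N therefore does not reveal a within-participant correlation. It also rests on the ANOVA, so the choice of non-parametric follow-up does not change it.

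**Step 2. Rank-sum against signed-rank on paired values.** Inputs: 45 pairs (section 2.3.3), a two-sided 5% level (5% is stated, two-sided is assumed), and an effect sized so that a paired t-test has the protocol's 95% power. The correlation ρ between the two members of a pair is an assumption and is varied.

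As an approximation, the unpaired statistic has variance 1 − ρ instead of 1, which gives:

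- actual type I error ≈ 2·[1 − Φ(1.960/√(1 − ρ))]
- power ≈ Φ(1.960 + 1.645 − 1.960/√(1 − ρ))

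At ρ = 0.5, 1.960/√0.5 = 2.772. The type I error is then 0.6%, and power is Φ(3.605 − 2.772) = Φ(0.833) = 80%. Simulation with normal data gives:

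| Assumed ρ | Rank-sum power | Signed-rank power | Rank-sum type I error |
|---|---|---|---|
| 0 | 95% | 94% | about 5% |
| 0.3 | 88–89% | 94% | about 2% |
| 0.5 | 77% | 94% | 0.5–1% |
| 0.7 | 50% | 94% | about 0.1% or less |

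Signed-rank type I error stays near 5% throughout. The loss is about 0, 5 to 6, 17 and 44 points in turn.

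Because this route is used only when normality fails, I also looked at lognormal data with the effect and correlation set on the log scale. Rank-sum versus signed-rank power is about 95% vs 92% at ρ = 0, 89% vs 91% at 0.3, 78% vs 90% at 0.5 and 49% vs 89% at 0.7. The pattern is the same and the gap is somewhat smaller.

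**Step 3. Which correlation applies to the primary outcome.** If the test is applied to pre-to-post changes, ρ is the correlation between the changes in two sessions, not between raw amplitudes. With equal variances and one common correlation r between any measurement in session A and any in session B:

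Cov(post_A − pre_A, post_B − pre_B) ∝ r − r − r + r = 0

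Simulation with 45 participants used pre/post and between-session correlations of 0.5/0.5, 0.7/0.7, 0.8/0.5 and 0.9/0.7. For changes, rank-sum power was 94–95% against 93–94% for signed-rank, and rank-sum type I error was 4.4–5.3%. Under this structure almost nothing is lost. A loss appears if participants who respond more in one session also respond more in another, since the changes are then positively correlated.

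For pre versus post comparisons of raw amplitudes within a session, no such cancellation occurs, and the table in step 2 applies directly.

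**The case against.** Three points can be made for the plan.

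**The wording may mean something else.** The text also speaks of analysis between groups, and there are six sequence groups of eight or nine independent participants, for which a rank-sum test would be legitimate. Or the authors may simply have meant signed-rank. The first reading fails because section 2.6.2 names the sessions, not the sequences, as what is compared, and because the pairwise hypothesis would then have no named test on this route. The second may be true, but an analyst following the text would run the unpaired test, so the sentence still needs correcting.

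**The damage is limited.** This stands. Only the fallback is affected; the Friedman test keeps the pairing and remains the overall test; the sample size is untouched; and with positive correlation the error is conservative, so it does not create false positives.

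**The loss may be small for the primary outcome.** This also stands. A reader might infer from the wrong test that power collapses, or that the true type I error is far below 5%. The protocol supports neither. Both need a sizeable correlation between session changes, which it does not report, and under equal correlation across all six measurements that correlation is zero.

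**Conclusion.** The stated follow-up test is wrong for the design, and it contradicts the matched test named in the same sentence. That conclusion needs no assumed numbers. It affects the only pairwise non-parametric test named for the trial's main comparisons.

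The consequence is a possible loss of power, of uncertain size. With 45 pairs and an effect sized for 95% paired power, it runs from nothing at correlation 0 to about 17 points at 0.5 and 44 points at 0.7. These correlations, the two-sided test and the data distributions are assumptions. For changes the loss may be close to nil; it is clearer for raw pre versus post comparisons. This is a should-fix point: a definite error, on a conditional route, with an easy remedy.

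**What to change.** In section 2.7, remove the rank-sum test and the phrase about independent variables. In their place, state that:

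- after the Friedman test, sessions will be compared with the Wilcoxon signed-rank test on within-participant between-session differences in pre-to-post MEP change: optimized minus conventional, optimized minus sham, and conventional minus sham if that pair is tested;
- these comparisons carry a multiplicity adjustment such as Holm, so that this route has the counterpart of Tukey's test on the parametric route;
- any pre versus post comparison within a session also uses the signed-rank test.

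The cost is one or two sentences, with no extra participants, visits or data. Section 2.9 reports that recruitment was still open. The change should be recorded before the data are analyzed, because switching tests afterwards would look driven by the results.

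### A normality test chooses the primary analysis, and the fallback is a Friedman test with no stated input plus an unpaired rank test; one pre-specified paired analysis of log amplitude would be better

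*Protocol article*

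**What the plan says.** All references are to the protocol article; no separate SAP is shown.

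- **Primary outcome (2.6.2):** "The difference between groups in MEP amplitude recorded before and after each tDCS session", measured over the M1 hand-knob.
- **Gate (2.7):** "The Shapiro–Wilk test will be employed to assess the normality of the data". It is not stated whether this means raw values, changes or model residuals.
- **Gate passed (2.7):** "If normality is met, a repeated measures ANOVA test will be used for within-and in-between groups analysis", with Tukey's test post hoc.
- **Gate failed (2.7):** "If normality is not met, the Friedman test will be used", accompanied by Wilcoxon rank-sum comparisons.
- **Design (2.1, 2.6.1):** each patient receives optimized, conventional and sham stimulation and is measured before and after each session, which gives six values per patient.
- **Scale (2.6.1):** amplitude is in microvolts, and no transformation is mentioned.
- **Sample size (2.3.3):** based on a within-between interaction, f = 0.2193764, 5% type I error, 95% power; 45 evaluable and 50 recruited.

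**The concern.** The outcome is a change compared across conditions, and the sample size was worked out for an interaction. A repeated measures ANOVA can carry a condition-by-time term. Friedman is a one-way test within patients and has no such term, so whether it addresses the primary question depends on what is put into it, and section 2.7 does not fix that. The follow-up test also ignores the pairing that the crossover provides.

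The two branches can therefore answer different questions, and the data decide which is asked. At stake is what a significant primary result would mean. If the six raw values were used, a rise common to all three sessions could be read as a treatment effect. If changes are used, the loss is power.

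**Working it through.** **1. The plan's own figure.** The article does not give the number of groups k, measurements m or correlation ρ. With k = 3, m = 6, ρ = 0.5 (inferred), λ = N·m·f²/(1−ρ) = 45 × 6 × 0.2193764²/0.5 = 25.99, with df (k−1)(m−1) = 10 and (N−k)(m−1) = 210. Power is 0.9545, and 45/0.9 = 50. The stated 45 and 50 are reproduced, and the target was an interaction, for which the fallback has no term.

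**2. How often the gate would fail.** The article gives no spread, so this is shown over a range. For one lognormal cell with n = 45 and CV = √(exp(s²)−1), where s is the log-SD:

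| log-SD | CV | Shapiro–Wilk rejects |
|---|---|---|
| 0.1 | 0.10 | 11% |
| 0.2 | 0.20 | about 30% |
| 0.3 | 0.31 | about 50% |
| 0.4 | 0.42 | about 75% |
| 0.6 | 0.66 | about 95% |

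The result also depends on how many sets of values are tested. With perfectly normal data, at least one of six independent tests rejects with probability 1 − 0.95⁶ = 26%, and at least one of three with 1 − 0.95³ = 14%.

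**3. What the fallback tests.** Assumed setting: n = 45, lognormal, log-SD 0.7 between patients, 0.25 between sessions, 0.25 residual. With a common log rise of 0.15 from pre to post and no treatment difference:

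- Friedman on the six values rejects in about 83% of trials.
- Friedman on the three within-patient changes rejects in about 4.5%.

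Four other assumed spreads gave 89–100% for six values and 3.9–4.9% for three changes. With smaller common rises (0.1 to 0.2 SD), the six-value version rejected in 11–30% of trials at correlation 0.5 and 20–71% at 0.8.

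**4. Power when changes are used.** Same setting, with assumed effects of +25% optimized, +10% conventional and 0 sham. The gate is applied to the three raw changes.

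- Gated plan: about 62% omnibus power by simulation.
- ANOVA on log change: about 77% by simulation. Formula check: log effects 0.2231, 0.0953, 0; sum of squares about their mean 0.02507; variance of a log change 2 × 0.25² = 0.125; λ = 45 × 0.02507/0.125 = 9.03; df 2 and 88; power 76%.

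With assumed log effects 0.30/0.15/0, the log analysis against the gated plan gave 0.996 v 0.983, 0.84 v 0.72, 0.59 v 0.45 and 0.41 v 0.30 at total log-SD 0.39, 0.62, 0.94 and 1.17.

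**5. Rank-sum on paired data.** Two conditions compared on post-session values, assumed log effect 0.2, total log-SD 0.39, 0.62, 0.94: rank-sum power is 0.74, 0.23, 0.04, against 0.96, 0.65, 0.42 for signed-rank. Type I error of rank-sum is 0–0.3%. The unpaired test is very conservative here because it leaves between-patient variation in the comparison.

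**The case against.** The strongest reply is that section 2.6.2 defines the outcome as a before/after difference, so the natural Friedman input is the three changes. On those, the test addresses the primary question at the correct level. This stands. A reader might infer that Friedman cannot test the effect at all, or that a false-positive rate of 11–71% or more is built into the plan; the article nowhere says that six columns are used, so neither follows.

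A reader might also infer that the gate will almost always fail. The article gives no SD, CV or skewness; at a CV of 0.2 to 0.3 a single cell fails only about 30–50% of the time. Nor does the gate itself inflate type I error: run on changes it gave 4.5–5.4% under the full null. A larger power gap can be produced by setting a raw paired test of change against a log analysis that also adjusts for baseline (about 28% v 48%), but that alters scale and adjustment together; for optimized versus conventional, the log scale alone moves the paired t-test from 28% to 39%, and signed-rank on raw change already reaches 36%. Section 2.7 also promises means and confidence intervals, so it cannot be said that no estimate will be reported.

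Finally, an article may leave details to an SAP. That excuses silence on residuals, period terms or absent responses. It does not excuse what section 2.7 does fix: a data-driven choice of primary test, and an independent-samples test for paired conditions.

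**Conclusion.** The point holds in this form and should be changed. Two defects rest on the text alone: a normality test selects the primary analysis, and the fallback combines a Friedman test of unstated input with a test that ignores the pairing. The consequences are an uncertain primary hypothesis and probable loss of power; inflated error arises only if the six raw values are used.

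The sizes are conditional. The gain from a log-scale analysis over the gated plan on changes is about 15 percentage points (77 − 62) in the setting used, and 1 to 14 points in the four other settings. All of these assume lognormal amplitudes with spreads and effects that the article does not supply. If amplitudes are close to symmetric, that advantage cannot be assumed, but the case for naming one primary analysis and using paired tests remains.

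**What to change.** - Remove the Shapiro–Wilk gate.
- Name one primary analysis: log MEP amplitude at the hand-knob, either log(post/pre) or log post adjusted for log pre, comparing the three conditions within patient. Report geometric mean ratios with 95% CI.
- Check residuals by plot, without letting the check change the primary analysis.
- As sensitivity analyses, apply Friedman and Wilcoxon signed-rank tests, in place of rank-sum, to the three within-patient changes.
- State a floor for an absent post-session MEP, since the inclusion criteria (2.3.2) secure a measurable response only at entry, and vary that floor in a sensitivity check.

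The cost is wording, to be settled before unblinding; recruitment was still open at publication (2.9). Effects will be read as ratios rather than microvolts, and a substituted floor can become an extreme value on the log scale, which is why it needs its own check. The log scale is not the only defensible choice, but it must be fixed in advance.

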### Safety, protocol, and data monitoring

2.8

During and 30 min after stimulation, the researchers will verify whether any adverse events related to tDCS, such as fatigue, dizziness, and redness, will present. If any adverse events occur, they will be assessed by a physician, classified according to severity criteria (mild, moderate, and severe), and report to the Institutional Review Board (IRB).

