Although the use of computational modeling in research and clinical practice has been recommended, its use has been scarce because it requires numerous software packages and professionals to create 3D head models and perform E-field calculations, which consumes time and resources (Yoo et al., 2022; Lee et al., 2023). Furthermore, accurate creation of a 3D head model is crucial for calculating tDCS-influenced E-field, especially as the segmentation of stroke-affected tissue directly affects the strength and orientation of the E-field in the target area (Lee et al., 2023). Recently, software capable of constructing a 3D realistic head model and accurately calculating the tDCS-induced E-field in patients with stroke in a relatively short period of time has been developed. This software allows the user to determine the optimal electrode position for each individual according to brain structure, stroke lesion, electrical conductivity, and electrode properties (Yoon et al., 2023).

Therefore,, the aim of the present crossover randomized control trial is to determine the immediate effect of personalized tDCS electrode positioning on the activation of the cortical region responsible for finger movement in patients with sub-acute or chronic stroke using MEP. Our hypothesis is that compared to conventional and sham stimulation, personalized electrode positioning will show changes in MEP amplitude over the cortical region responsible for finger movement in this population. Furthermore, we hypothesize that the participants would tolerate the tDCS sessions without experiencing any significant adverse events. We aim to reduce the inconsistencies in tDCS intervention in patients with stroke and to improve motor function in these patients, especially in the upper extremity.

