**Figure 1 fig1:**
[figure not shown]
Study design. Group participants randomization into six groups for the purpose of the three different types of tDCS intervention: 1-1, 2-1, 2-2, 3-1, 3-2. MEP, motor-evoked potential; tDCS, transcranial direct current stimulation; V, visit.

**Table 1 tab1:** Schedule of enrollment, interventions, and assessments.

Schedule	Screening	Baseline	Wash-out (>24 h)	Assessment	Wash-out (>24 h)	Assessment
visit (V)	V1	V2		V3		V4
Written consent	V					
Demographic information	V					
Medical and surgical history	V					
Eligibility screen	V	V				
Vital signs screen	V					
Physical examination	V					
MRI examination	V					
Randomization		V				
tDCS application		V		V		V
MEP examination	V	V		V		V
Adverse events examination		V		V		V
Allowed medication and therapies screening		V		V		V

MEP, Motor-evoked potential; MRI, Magnetic resonance imaging; tDCS, transcranial direct current stimulation.

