However, this study presents some limitations. First, only the immediate effects of tDCS will be evaluated as the participants will be assessed immediately after the application. Therefore, the short-and long-term effects of tDCS should be investigated in future studies. Second, the study will include and analyze data combined from patients with sub-acute or chronic stroke, which should be interpreted independently in future research to determine the effect of optimized tDCS electrode locations according to each stroke phase. Furthermore, inclusion of patients with acute stroke is necessary. Third, the study sample includes participants within a wide age range (young and older adults), which may influence the results.

As expressed before, we hypothesize that the optimized active tDCS session will show a greater increase in MEP over the cortical region responsible for finger movement in patients with sub-acute or chronic stroke than conventional and sham tDCS sessions. Additionally, we hypothesized that participants would tolerate the tDCS sessions without any significant adverse events.

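### Tolerability is hypothesised without a time limit, but the described adverse event check ends 30 min after stimulation and nothing is scheduled after the last session

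*Protocol article*

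**What the plan says.** Tolerability is stated as a hypothesis twice. The Introduction says "we hypothesize that the participants would tolerate the tDCS sessions without experiencing any significant adverse events", and the Discussion repeats that "we hypothesized that participants would tolerate the tDCS sessions without any significant adverse events". Neither sentence gives a time limit.

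The method of finding events is in section 2.8: "During and 30 min after stimulation, the researchers will verify whether any adverse events related to tDCS" are present, with fatigue, dizziness and redness as examples. Events found go to a physician, are graded for severity and are reported to the IRB.

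In Table 1 the row "Adverse events examination" is marked at V2, V3 and V4. Each of these is a stimulation visit, with a wash-out of more than 24 h between them, and V4 is the last column. Section 2.1 describes the sequence: "After a 24-h washout period, the groups will cross to receive a different tDCS intervention until each group receives all three alternatives".

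Adverse events are not among the primary or secondary outcomes (sections 2.6.2 and 2.6.3), and section 2.7 gives no test or margin for tolerability.

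**The concern.** The stated observation window is narrower than the stated hypothesis. A conclusion that the sessions were well tolerated would be read as covering what participants experienced because of the session, including a skin reaction, headache or fatigue that appears that evening or the next day. The described check would not see such an event. If it is lost, the reported event rate is too low; loss of this kind cannot make it too high.

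There is also a question of attribution. With sessions about a day apart, an event mentioned at V3 or V4 may have begun after the previous session. The article gives no rule that keeps it from being recorded against the session given that day, which is a different condition.

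**Working it through.** **Inputs.** Group sizes (section 2.1): four groups of 8 and two of 9. Three sessions per participant (section 2.1). Recruitment target 50, from 45 with 10% dropout (section 2.3.3). Visits with an adverse event examination: V2, V3, V4 (Table 1). The rate of delayed events is not given, so a range of 2% to 20% per session is assumed for illustration only.

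**The article's own count.** 4 × 8 + 2 × 9 = 32 + 18 = 50, and 45 / (1 − 0.10) = 50. Both agree with the stated target.

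**Sessions with no later visit.** Planned sessions: 50 × 3 = 150. The third session of each participant is followed by no visit: 50 / 150 = one third. This assumes that everyone completes. A participant who leaves early also has a last session with nothing after it.

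**Split by condition.** Taking the six groups as the six possible orders of three conditions, each condition is last in two groups. The number is 8 + 8 = 16, 8 + 9 = 17 or 9 + 9 = 18, depending on where the two groups of 9 fall. The three conditions then split as 16, 16, 18 or as 16, 17, 17.

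**What is described for each session.**

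| Session | During and to 30 min after | Next contact | Does the text say it looks back? |
|---|---|---|---|
| 1 (V2) | yes | V3, more than 24 h later | no |
| 2 (V3) | yes | V4, more than 24 h later | no |
| 3 (V4) | yes | none scheduled | not applicable |

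**Expected number of delayed events missed,** for an assumed rate q per session:

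| q | V3 and V4 look back: 50 × q | They do not: 150 × q |
|---|---|---|
| 2% | 1.0 | 3.0 |
| 5% | 2.5 | 7.5 |
| 10% | 5 | 15 |
| 20% | 10 | 30 |

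If q is the same in all conditions, the losses after the last session differ between two conditions by at most (18 − 16) × q, which is 0.04 events at 2% and 0.4 events at 20%.

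**What a clean result would show.** If none of 50 participants has an event, the one-sided 95% upper limit for the proportion affected is 1 − 0.05^(1/50) = 5.8%; with 45 participants it is 1 − 0.05^(1/45) = 6.4%. Either limit applies only to events that the check can detect.

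**The case against.** The best defence is that section 2.8 says when researchers actively look and does not say that later or spontaneous reports are ignored. This is a condensed article, and the full protocol may define a longer reporting period. The hypothesis is about tolerating the sessions, which is largely what is observed. The Discussion also admits that "only the immediate effects of tDCS will be evaluated as the participants will be assessed immediately after the application". Tolerability is not an endpoint and has no test.

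Much of this stands, and it rules out three stronger readings.

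- A reader might infer that delayed events go uncounted after all 150 sessions. The documents do not show this: V3 and V4 carry an examination more than a day after sessions 1 and 2. They leave open whether it looks back.
- A reader might infer that only events already judged to be caused by tDCS are recorded. The wording with its examples can as well name the kinds of event sought, and the next sentence sends any adverse event to a physician.
- A reader might infer a bias between active and sham. The same window applies to every condition, last sessions are almost evenly spread, and no comparison of safety between conditions is planned. The gap does not by itself create a difference.

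The remaining defence does not close the gap. The article gives a specific window and a full visit schedule, and these do not reach as far as its hypothesis. The admitted limitation concerns the effects of tDCS in general, and the tolerability hypothesis restated shortly afterwards is not limited to match.

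**Conclusion.** The point holds in a limited form. For the last session, 50 of 150 sessions and 16 to 18 per condition, the article describes no way to record an event that starts after the 30-min check. For sessions 1 and 2 a route may exist, but neither the look-back nor the attribution is stated. The direction of any error is known, an undercount of the absolute event rate. The size is not known, because the documents give no delayed-event rate; the figures of 1 to 10 or 3 to 30 missed events rest entirely on the assumed 2% to 20%. The counts assume full completion and that the six groups are the six possible orders. The primary MEP analysis is not affected. The point deserves correction because the remedy is cheap and the tolerability claim would otherwise reach beyond what was observed.

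**What to change.** In section 2.8 and Table 1, state that at the start of V3 and V4, before stimulation, participants are asked about all adverse events since the previous session, whether or not they seem related. Attribute those events to the previous session, and report events by session type.

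For the last session, choose one of two courses: make one short telephone contact after V4 for participants still to be treated, or word the tolerability conclusion as covering only the stimulation period and the 30 min after it. Participants who have already finished can be covered only by the second.

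The cost is one question at two existing visits and at most 50 short calls, fewer because recruitment began in September 2022 (section 2.9). A few more unrelated events will be recorded. Ascertainment will differ between earlier and later participants, and the report should say so. Stimulation and treatment stay as they are.
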